
**Objectives**

The specific goals of the study are

1. to verify the virological non-inferiority after 48 weeks of the treatment simplification from a "standard" combination antiretroviral therapy including 3 drugs to Maraviroc (MVC) plus Darunavir/ritonavir QD, in patients virosuppressed from 24 weeks showing any grade toxicities to ongoing treatment or willing to reduce drug or need to simplify therapy or NRTI sparing regimen
2. to collect relevant information about the safety, the immunologic and the economic impact of this strategy

**Study design**

This is a 2-arm, prospective, multicenter, open- label, 1:1 randomized controlled trial. The number of patients planned to be included is 330 (165 per arm). The expected duration of the study include 6 months for enrollment, 28 days of screening at baseline, 96 weeks of treatment (48 weeks for the primary endpoint) and 30 days of follow-up after the end of the study. In case of virological failure (defined as the occurrence of 2 consecutive HIV-RNA above 50 copies / mL or a single value greater than 1000 copies / mL) therapy will be modified guided by resistance genotype and discontinuation of the CCR5 antagonist; in case of no genotyping for low levels of viremia (or other technical reasons) the new regimen will include at least one PI / r associated with drugs selected on the basis of best clinical judgment.

Drugs will be distributed by outpatients structures and batch and expiration date of each package of medication delivered will be recorded.

**Eligible subjects**

• males and females >/= 18 years of age

• HIV infected with R5 tropism by viral DNA genotyping (geno2pheno "clonal")

• treated with the same HAART regimen including 3 drugs from at least 4 months

• with at least two viral load < 50 copies/mL in two consecutive determinations at least 6 months apart (tolerance of two weeks)

• with CD4 cell count > 200 cells/μL and without any opportunistic infection or AIDS-related disease for at least one year prior to the screening

• who gave informed consent to the participation to the study.

**Non eligible subjects**

• With at least one major or two minor mutations conferring resistance to darunavir reported in the update list of International AIDS Society - USA , in previous resistance tests. Previous determination of D/M or X4 viral tropism

• Previous major clinical toxicities (grade >=3) to the proposed drugs of the study

• Pregnancy or breast feeding, desire of pregnancy in the short term

• Past exposure to CCR5 antagonist

• HBsAg positive serostatus

• Liver cirrhosis of class C (Child-Pugh)

• Sulpha drug hypersensitivity

• The presence of major non AIDS-defining diseases that, in the opinion of the investigator, may compromise the retention of the patient in the study for the necessary follow-up period.

• Estimated glomerular filtration < 30 ml/min (Cockroft-Gaut; MDRD if black-African or african-american) at screening visit

•Hypertransaminemia of grade IV (more than 10 times the upper normal limit) at screening visit

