**Study assessment and procedures**

**Screening visit**

During screening visit will be obtained written informed consent, patients medical history collection and treatment (antiretroviral or not) with complete registration of all concomitant medications, the search for markers of HBV and HCV infection, pregnancy test for women of childbearing age or serum FSH dose for women in menopause for less than 2 years, complete physical examination of vital signs, weight and height, blood tests (liver and kidney function, fasting glucose, complete lipid profile, amylase, Na, K, P , Ca, Cl, CK, uric acid), complete blood count, complete urinalysis, lymphocyte immunophenotyping, HIV-RNA. Will also be determined the genotypic tropism of HIV-V3 from viral DNA extracted from whole blood by sequencing.

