**Baseline**

The day the simplified therapy with maraviroc, darunavir / ritonavir will be administered for the first time will be defined as baseline (day 0); in the control group the baseline will be represented by the first visit after the randomization . The physical examination should be repeated along with the determination of vital signs, weight and height, blood tests (liver function, including ALT, AST, tot bil / alkaline phosphate and gammagt, and kidney, fasting glucose, complete lipid profile, amylase, lipase, Na, K, P, Ca, CK), the complete blood count, urine examination complete, the lymphocyte immunophenotyping, HIV-RNA, and set aside a plasma sample and a sample of whole blood for 'genotype analysis of V3 on RNA and DNA, respectively. Furthermore, additional analysis will be performed on the bone metabolism (alkaline phosphatase, calcitonin, parathyroid hormone, osteocalcin, dose of vitamin D3, urinary hydroxyproline, urinary hydrossiploline).

Renal function is monitored by calculation of the CG or MDRD and the measured creatinine clearance, 24 hours proteinuria, natriuria, Kaliuria, calciuria, phosphaturia, chlorides and uricuria 24 hours.
Fasting insulin levels will also be assessed at baseline. In specific subgroups subcutaneous fat on the face, arm and thigh will be measured by ultrasound (Liposound); the average intima media thickness (IMT), carotid Doppler ultrasound, endothelial function by flow-mediated dilation (FMD) of brachial artery and bone mineral density and distribution of subcutaneous fat by DEXA will also be measured.

Finally, patients will be asked to complete a self-reported adherence questionnaire, a self-reported questionnaire on symptoms and quality of life and will undergo an evaluation of basic neurocognitive screening tests, and if necessary based on the screening tests, a more in depth evaluation using extensive neurocognitive assessment batteries. On the same day candidates will be subjected to the patients randomized 1:1 in the following arms:

A) * Maraviroc 300 mg (1 tablet) every 24 h + 800 mg darunavir (2 400 mg tabs) every 24 h + ritonavir 100 mg (1 heat stable tablet) every 24 h in the morning (in order to make TDM)
B) Continuation of previously ongoing treatment

* 150 mg (1 tablet) every 24 h if estimated creatinine clearance <80 ml ​​/ min

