**Monitoring**

The monitoring visits will be organized at 4, 12, 24, 36, 48, 60, 72, 84 and 96 weeks.
At each visit monitoring will include blood chemistry tests (all lipids, transaminases, tot/conjugated bilirubin, amylase creatinine, Na, K, P, CK, fasting glucose, plasma) and blood cell counts, urinalysis, lymphocyte subsets and viral load of HIV, monitoring of plasma concentrations of maraviroc, darunavir and ritonavir at 24 + / - 2h (NB patients in arm A should be instructed not to take the study medication prior to sampling).
Monitoring of renal function by MDRD or CG will be repeated at all visits, while the creatinine clearance, proteinuria of 24 hours, natriuria, Kaliur, calciuria, phosphaturia, chlorides and uricuria of 24 hours will be measured at week 24, 48 72 and 96.
The assessment of fasting insulin and markers of bone metabolism (alkaline phosphatase, calcitonin, parathyroid hormone, osteocalcin, vitamin D, calciuria and phosphaturia urinary hydroxyproline) will be repeated at 24, 48 and 96 weeks, measuring subcutaneous fat on the face, arms, thighs and the average intimal thickness (IMT) and DEXA for bone densitometry will instead be repeated at 48 and 96 weeks. The questionnaire on self-reported adherence will be repeated at each visit; the questionnaire on self-reported symptoms and quality of life will be administered to 4, 24, 48 and 96 weeks, while the assessment of neurocognitive tests (battery of screening tests for investigation and possible pathological) will be repeated at week 48 and 96.
In case of virological failure (occurrence of 2 consecutive HIV-RNA above 50 copies / mL or a single value greater than 1000 copies / mL) a genotypic resistance test on plasma viral RNA will be performed within one month from the observation. At each visit, a plasma sample for the V3 genotype and resistance to HIV and a sample of whole blood for analysis of viral DNA will be stored for possible future evaluation as judged by the principal investogator of the study. The flow chart of the visits is attached to the document (Annex 1). Blood chemistry, hematology and microbiological studies will be performed under the clinical routine and without additional costs for the structure.
The therapeutic plasmatic drug monitoring will be carried out in collaboration with the Institute of Pharmacology (Clinical Pharmacology Service) of the Gemelli Hospital.

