**STUDY ASSESSMENT AND PROCEDURES**

**Flow-chart/Time and Events Schedule**

| **Procedures** | **Screening**  **(day -28)** | **Basale**  **(giorno 0)** | **Follow-up visit (weeks 4, 12, 36)** | **Follow-up visit (week**  **24)** | **Follow-up visit (week 48)** | **Follow-up visit**  **(week s**  **60, 72, 84)** | **Follow-up visit ( week 96)** | **Follow –up vist post-treatment**  **(after 30 days)** |
| --- | --- | --- | --- | --- | --- | --- | --- | --- |
| Written informed consent | **X** |  |  |  |  |  |  |  |
| Medical history | **X** |  |  |  |  |  |  |  |
| Therapeutic history | **X** |  |  |  |  |  |  |  |
| Concomitant medication use | **X** | **X** | **X** | **X** | **X** | **X** | **X** | **X** |
| HBsAg ed anti-HCV | **X** |  |  |  |  |  |  |  |
| Serum pregnancy test or serum FSH | **X** |  |  |  |  |  |  |  |
| Full physical examination, vital signs, height, weight | **X** | **X** | **X** | **X** | **X** | **X** | **X** | **X** |
| Blood exam and urine analysis | **X** | **X** | **X** | **X** | **X** | **X** | **X** | **X** |
| Urine analysis (24 hours) |  | **X** |  | **X** | **X** | **X****** | **X** |  |
| Hematology chemistry | **X** | **X** | **X** | **X** | **X** | **X** | **X** | **X** |
| Lymphocyte subsets and HIV RNA | **X** | **X** | **X** | **X** | **X** | **X** | **X** | **X** |
| Darunavir, ritonavir and maraviroc TDM (arm a)*** |  |  | **X** | **X** | **X** | **X** | **X** | **X** |
| Whole blood sample for viral DNA genotyping | **x** | **X** | **X** | **x** | **x** | **x** | **x** |  |
| Blood sample for HIV resistance test ant tropism test | **(*)** | **(*)** | **(*)** | **(*)** | **(*)** | **(*)** | **(*)** |  |
| Fasting insulin, study of bone metabolism |  | **X** |  | **X** | **X** | **X** | **X** |  |
| **IMT, FMD, body fat |  | **X** |  |  | **X** |  | **X** |  |
| **Bone DEXA |  | **X** |  |  | **X** |  | **X** |  |
| Adherence self-reported questionnaire |  | **X** | **X** | **X** | **X** | **X** | **X** |  |
| Symptoms questionnaire and QoL |  | **X** | **X (only week 4)** | **X** | **X** | **X** | **X** |  |
| **Neurocognitive test |  | **X** |  |  | **X** |  | **X** |  |

(*) sample storage at -20°C and for analysis in virological failure (two consecutive measures of HIV-RNA higher than 50 copies/mL or a single measure higher than 1000 copies/mL)

** in selected participating centers

*** TDM in 20 patients at week 4 with 9 points of determination **** at week 72

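### Pregnancy is an entry exclusion, but the only scheduled pregnancy test is at screening: none at baseline before randomisation, and none at the nine visits over 96 weeks

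*Combined protocol and SAP*

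**What the plan says.** Under Non eligible subjects, the protocol excludes "Pregnancy or breast feeding, desire of pregnancy in the short term". The Screening visit section provides a "pregnancy test for women of childbearing age or serum FSH dose for women in menopause for less than 2 years". In the Flow-chart/Time and Events Schedule this is a row of its own, "Serum pregnancy test or serum FSH", with one mark, in the day -28 column. The cells for baseline, every follow-up visit and the 30-day post-treatment visit are empty.

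The Baseline section lists the day-0 procedures in detail, including "the complete blood count, urine examination complete", and names no pregnancy test. It places randomisation on that day: "On the same day candidates will be subjected to the patients randomized 1:1 in the following arms". For follow-up, "The monitoring visits will be organized at 4, 12, 24, 36, 48, 60, 72, 84 and 96 weeks". The Monitoring section lists chemistry, blood counts, urinalysis, lymphocyte subsets, viral load and drug levels, again with no pregnancy test. The flow chart plans "Full physical examination, vital signs, height, weight" at every visit.

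Criteria for exit from the study does not name pregnancy. Unscheduled visits lets the investigator recall a patient for safety, and Exit from the study lets the investigator exclude a patient whose health is at risk.

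**The concern.** The plan treats pregnancy as a reason not to enter the trial, yet checks it once and early. A site following the protocol exactly could randomise and dose a woman who conceived after her screening test, and could continue her on study for up to 96 weeks with no planned step that looks for pregnancy. No section says what to do when a pregnancy is found.

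What is at stake is the safety of participants, and the check of one eligibility criterion on the day it matters. The trial's inference is not threatened.

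**Working it through.** **1. Count of scheduled tests.** Text and flow chart agree.

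| Time point | Pregnancy tests scheduled |
|---|---|
| Screening (day -28) | 1 |
| Baseline (day 0, randomisation) | 0 |
| Weeks 4, 12, 24, 36, 48, 60, 72, 84, 96 | 0 of 9 |
| 30 days after treatment | 0 |

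The row "Blood exam and urine analysis" does not cover the test, because the pregnancy test has a separate row with its own single mark.

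**2. Expected pregnancies.** The documents give 165 patients per arm, 28 days of screening and 96 weeks of treatment. Everything else is assumed: 20-30% women, 50-70% of them able to conceive, and 0.01-0.05 pregnancies per woman-year. The low end of the rate allows for the exclusion of women who want a pregnancy soon.

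- Women at risk per arm: 165 × 0.20 × 0.50 = 16.5, to 165 × 0.30 × 0.70 = 34.65.
- Pregnancies per arm in 96 weeks: 16.5 × 0.01 × 96/52 = 0.30, to 34.65 × 0.05 × 96/52 = 3.20.
- Chance of at least one per arm: 1 − exp(−0.305) = 26%, to 1 − exp(−3.198) = 96%. The upper figure puts all three assumptions at their maximum.
- Screening to first dose (4 weeks): 16.5 × 0.01 × 4/52 = 0.013, to 34.65 × 0.05 × 4/52 = 0.133. This is 4/(4 + 96) = 4% of the total.

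**3. Time gained by testing at visits.** Let conception time t be uniform over weeks 0 to 96, let clinical recognition come D weeks after conception, and let a test be positive from 2 weeks after conception. Undetected time is counted to week 96.

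- Present schedule: mean of min(D, 96 − t).
- With tests: mean of min(D, wait from t to the first visit at or after t + 2, 96 − t).

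| D (weeks) | Mean now | Mean with tests | Gain (weeks) | Found earlier |
|---|---|---|---|---|
| 4 | 3.92 | 3.75 | 0.17 | 17% |
| 6 | 5.81 | 5.17 | 0.65 | 31% |
| 8 | 7.67 | 6.25 | 1.42 | 46% |
| 12 | 11.25 | 7.44 | 3.81 | 73% |
| 16 | 14.67 | 7.58 | 7.08 | 85% |

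If a test turns positive only 3 weeks after conception, the gain at D = 6 falls from 0.65 to 0.35 weeks. For conceptions up to week 94, the longest wait to a positive scheduled test is 12 + 2 = 14 weeks. Later conceptions would not be caught by week 96.

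**4. Effect on the primary endpoint.** By week 48 the expected pregnancies per arm are 16.5 × 0.01 × 48/52 = 0.15, to 34.65 × 0.05 × 48/52 = 1.60. Even if every one led to a switch counted as failure, that is 0.15/165 = 0.09 to 1.60/165 = 0.97 percentage points in an arm, against a margin of 10 points.

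**The case against.** Pregnancy appears only as an entry criterion. No section says that a woman who conceives on study must stop, and text and flow chart agree on one eligibility test. A reader might infer that the protocol contradicts itself, or that it forbids continuing in pregnancy. The documents support neither. The missing follow-up tests are a gap in safety monitoring. Only the baseline test bears on the plan's own criterion, and that window holds about 4% of the expected pregnancies.

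A reader might also infer a known fetal risk from the study drugs, or demonstrated harm. The documents do not say why pregnancy is excluded, and weeks undetected is a process measure. Earlier detection permits an earlier decision; these documents cannot show that it changes outcomes.

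The benefit could be small. Women entering have no short-term wish for pregnancy and are examined and weighed every 4 to 12 weeks. If a woman recognises a pregnancy 4 weeks after conception, testing gains about one day on average. This stands, and it sets the low end of the range. Multiplying the extremes, 0.30 × 0.17 to 3.20 × 7.08, gives about 0.05 to 23 undetected weeks avoided per arm, a spread that comes entirely from assumptions.

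Contraception or reporting duties may sit in consent material or pages not available here. They could lower the risk, but they would not add a test to this schedule. Investigator discretion is a real safeguard, but only once someone suspects a pregnancy.

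Finally, arm B continues its previous treatment, so the argument about starting a new regimen does not reach it. Testing both arms is justified by equal follow-up, and the entry exclusion applies to both.

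**Conclusion.** The point holds as a worthwhile, low-cost safety improvement. The schedule itself is certain: one test at screening, none at baseline, none at nine monitoring visits. The size is uncertain and rests wholly on assumed rates: about 0.3 to 3.2 pregnancies per arm over 96 weeks, found on average about 0.2 to 7 weeks earlier if recognition would take 4 to 16 weeks and a test is positive 2 weeks after conception. The gain is less if tests turn positive later.

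A reader might infer that undetected pregnancies could distort the non-inferiority result. At no more than about 1 point against a 10-point margin, under the most unfavourable assumptions, they would not. The planned intention-to-treat analyses already count switches both as failures (S = F) and, with undetectable viral load, as non-failures (S ≠ F). No further analysis is needed.

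**What to change.** For women of childbearing potential in both arms:

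1. **Baseline section and flow chart:** add a rapid urine pregnancy test on the urine already collected, read before randomisation and first dose. A woman who tests positive is not randomised.
2. **Monitoring section and flow chart:** add a urine or serum test at weeks 4, 12, 24, 36, 48, 60, 72, 84 and 96 on samples already collected. Confirm any positive result before acting on it.
3. **Exit from the study:** state that a confirmed pregnancy triggers a documented individual treatment decision, without interrupting antiretroviral therapy.

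The cost is one amendment and about ten inexpensive assays per woman at risk. Under the assumptions above, that is 33 × 10 = 330 to 69.3 × 10 = 693 assays over both arms, with no added visit. The drawbacks are occasional false positives and possibly a few more recorded switches, at most the 0.15 to 1.6 pregnancies per arm assumed by week 48.

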**Criteria for exit from the study**

Virological failure, defined as the occurrence of 2 consecutive HIV-RNA above 50 copies / mL or a single value greater than 1000 copies / mL.

Diagnosis of opportunistic infection or other HIV-related disease or serious adverse events associated with drugs administered to the patient

Grade 4 laboratory abnormalities at monitoring exams (except for lipids)

Major protocol violations

Withdrawal of informed consent

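### Screening sets only two laboratory toxicity limits, yet any non-lipid grade 4 value from week 4 is an exit criterion, so a patient already at that threshold can be randomised

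*Combined protocol and SAP*

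**What the plan says.** Entry. Under Non eligible subjects, two bullets set a laboratory toxicity limit at screening: "Hypertransaminemia of grade IV (more than 10 times the upper normal limit) at screening visit" and "Estimated glomerular filtration < 30 ml/min". The bullet on previous grade 3 or higher toxicity covers clinical toxicity to the study drugs only. Under Objectives, the target population includes patients "showing any grade toxicities to ongoing treatment". Eligible subjects asks that they be "treated with the same HAART regimen including 3 drugs from at least 4 months".

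Exit. Criteria for exit from the study lists "Grade 4 laboratory abnormalities at monitoring exams (except for lipids" as a reason to leave, with no exemption for a value present at entry. Under Monitoring, "The monitoring visits will be organized at 4, 12, 24, 36, 48" weeks and onwards. The analytes include "tot/conjugated bilirubin, amylase creatinine, Na, K, P, CK, fasting glucose", with transaminases and blood counts.

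Arms and endpoint. Arm B is "Continuation of previously ongoing treatment". Under Primary Endpoint, stopping or adding a drug counts as failure in either arm.

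**The concern.** The plan applies one grade 4 threshold to transaminases at entry and a much wider one after entry. The trial recruits patients with toxicity on their present regimen and assigns half of them to stay on it. A value that the plan treats as grounds to leave can therefore be known before randomisation and still not bar entry.

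Two things are at stake. The first is safety: a patient may be assigned to continue a suspected drug at a grade that the plan itself regards as a reason to stop participation. The second is interpretation: if such exits involve a drug change and fall mainly on controls, they lower the control success rate for a reason fixed before randomisation and unrelated to virological efficacy. In a non-inferiority comparison that favours the new regimen.

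**Working it through.** **1. Entry and exit side by side**

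| Laboratory value | Bars entry at screening? | Exit criterion from week 4? |
|---|---|---|
| Transaminases, grade 4 | Yes | Yes |
| eGFR below 30 ml/min | Yes | If the renal value is grade 4 |
| Bilirubin, amylase, CK, glucose, electrolytes, blood counts, grade 4 | No | Yes |
| Lipids, grade 4 | No | No (exempt) |

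The gap is the third row. Child-Pugh class C cirrhosis and the investigator's judgement on major non-AIDS disease (Non eligible subjects), unscheduled visits for laboratory abnormalities (Unscheduled visits) and removal for risk (Exit from the study) may catch some of these patients, but none sets a laboratory limit at entry. Day-0 bloods cannot act as a filter, because the Baseline section places randomisation on the same day.

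**2. The plan's sample size**

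Inputs from Statistical analysis and sample size calculation: 90% control success, margin 10 points, 80% power, 5% loss, 165 per arm. The two-proportion formula for 90% against 80%, one-sided 0.05, gives 157 per arm, and 157 × 1.05 = 164.9, so 165. The point does not depend on this figure. Going the other way, 165 × 0.95 = 156.75, so 157 evaluable per arm is used below.

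**3. Effect if the exits count as failures**

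The documents give no frequency, so the shares are assumptions. Let x be the share of controls who exit with a drug change because of a value present at entry, and f the arm A share relative to control. Take true virological success as 90% in control and 80% in arm A, a difference exactly at the margin. Observed success is then 0.90 × (1 − x) in control and 0.80 × (1 − f·x) in arm A. Non-inferiority is declared when the lower bound of the Wald 95% interval exceeds −10 points. Exact binomial enumeration gives this probability of declaring it:

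| x | f = 0 | f = 0.5 | f = 1 |
|---|---|---|---|
| 0 | 2.73% | 2.73% | 2.73% |
| 1/157 (one control) | 3.73% | 3.24% | 2.81% |
| 1% | 4.41% | 3.56% | 2.86% |
| 2% | 6.77% | 4.55% | 2.99% |
| 3% | 9.93% | 5.73% | 3.12% |

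**4. What those rates are measured against**

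With f = 0, the difference on the composite endpoint (virological failure or switch) is 0.80 − 0.90 × (1 − x):

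- x = 1%: 0.80 − 0.891 = −9.1 points
- x = 2%: 0.80 − 0.882 = −8.2 points
- x = 3%: 0.80 − 0.873 = −7.3 points

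All lie inside the margin. If the composite difference is instead held at exactly −10 points with the same control rates, the probability is 2.70%, 2.68% and 2.66%.

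**5. Effect if the patients are left out of the per-protocol set**

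The plan does not say how grade 4 exits are handled there. Dropping k affected controls (157 against 157 − k) gives, for k = 1 to 5, a false non-inferiority rate of 2.69%, 2.72%, 2.66%, 2.77% and 2.67%. Power at 90% in both arms is 83.9%, 83.6%, 83.3%, 84.1% and 83.7%, against 84.2% with none dropped. The sequence is not monotone because the counts are discrete.

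**The case against.** The strongest reply is that the composite endpoint counts a drug stop or addition as failure on purpose. A control who has to stop a toxic drug has failed on that endpoint, so a reader who takes 4.4-9.9% as an inflated type I error on the primary endpoint would be wrong. Step 4 of the working bears this out, and the reply stands. The rates are errors only with respect to a purely virological question, on which the secondary intention-to-treat analysis that does not count switches with undetectable viral load as failures would partly show the effect.

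A reader might also infer that such a patient already meets the exit rule when randomised. The text does not support that: the rule applies at monitoring exams, so at screening the patient is only at its threshold. Nor does the effect always favour the new regimen. Eligible subjects does not bar patients already on darunavir/ritonavir, which arm A keeps, and values with another cause can persist in both arms.

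The affected group may well be very small. It needs a grade 4 value outside the two barred categories, a clinician and patient who still accept randomisation, persistence to week 4, and an exit with a drug change. At least four months on the same regimen means that many severe values would already have prompted a switch. Arm B adds no new drug, and unscheduled visits and removal for risk allow prompt action. This limits the size of the problem and the safety concern, but these protections are discretionary and do not close the gap in the entry rule.

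Finally, a single unconfirmed screening value, such as a transient CK rise, would exclude, and the plan names no general grading scale. Both are fair, but the existing exit rule has the same limits.

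**Conclusion.** The mismatch between the entry and exit rules is real in the current text and does not depend on any calculation. Its effect on the result is conditional. It requires that such patients exist, that their exits involve stopping or adding a drug, that they are scored as failures rather than left out of the per-protocol set, and that the causal drug is one that arm A stops. Under all four conditions, and with arm A unaffected, the composite result moves towards non-inferiority by 0.9 points for each 1% of controls affected. Against a true virological difference of −10 points, the chance of declaring non-inferiority goes from 2.7% to 4.4%, 6.8% or 9.9% for 1%, 2% or 3%. With equal shares in both arms it is 2.9-3.1%. If the patients are left out of the per-protocol set, the rate stays at about 2.7% and power falls by less than one point.

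The documents do not support reading this as a loss of type I error control on the planned endpoint, or as a demonstrated bias: the number affected is unknown and may be zero. The point stands as a low-priority, cheap improvement that aligns entry with the plan's own safety threshold.

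**What to change.** Under Non eligible subjects, widen the transaminase bullet to: *any grade 4 laboratory value except lipids at the screening visit (transaminases: more than 10 times the upper normal limit)*. Keep the eGFR limit. Under Objectives, qualify the any-grade toxicity phrase so that it agrees with this exclusion. Leave the grade 4 exit criterion as it is. Restricting it to new or worsening values would also remove the mismatch, but by weakening a safety rule.

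The cost is one bullet and one phrase. The bloods are already planned at screening: liver and kidney function, glucose, amylase, electrolytes, CK and blood count. The sample size does not change. The downside is that a few patients with severe laboratory toxicity, who are within the stated target population, cannot enter. A value that first reaches grade 4 between screening and day 0 would not be caught and would remain under the exit criterion.
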